### Assignment of Intervention

#### Allocation: Sequence Generation

Patients will be randomised using a validated and password-protected trial website, designed and supported by UK CRC registered Exeter Clinical trials unit (CTU).

#### Allocation Concealment

Patients will be allocated 1:1 to intervention or control and were stratified by centre using a web-based computer-generated random-allocation sequence to ensure concealment. This website will be password protected and managed by Exeter CTU.

#### Blinding

Patients, investigators, outcome assessors and analysts will all be blinded. Only two study nurses at each site will be unblinded to the treatment received by the participants.

#### Data Collection/Management

Data analyses will be conducted and reported in accord with CONSORT (Consolidated Standards Of Reporting Trials) guidelines for non-drug trials [28]. Participant flow will be summarised using a flow diagram, which will report recruitment and drop-outs and baseline patient characteristics and outcome scores reported and compared by group. The primary analysis for the primary and secondary outcomes will take an intention-to-treat approach based on a between-group comparison of intervention and control participants with complete data at 6 months, with adjustments being made for the baseline outcome score and centre. In a secondary analysis we will extend the primary analysis model with a repeated measures comparison of groups at all follow-up points. We comprehensively examine patterns and reasons for the missing outcome data and undertake appropriate imputation models to assess the impact of missingness on primary analysis models. Results will be reported for between-group mean differences and 95% confidence intervals. Safety outcomes will be reported descriptively by group. No correction of *P* values for multiplicity of testing will be undertaken. However, the primary outcome analysis will be performed before all other analyses, and the *P* values of all subsequent analyses will be interpreted in the context of multiple testing. No interim analyses are planned.

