### Sample Size

For our primary outcome of pain severity VAS (0-100 mm), the Initiative on Methods, Measurement and Pain Assessment in Clinical Trials (IMMPACT) proposes a minimally important clinical difference (MICD) of 20 mm [27]. To detect this MICD and based on a back/leg pain VAS standard deviation of 25 mm, as seen in previous conventional and 10Khz-SCS RCTs set at 90% power and 5% alpha, and a worst case attrition rate of 30% at 6-months follow up, we will need to recruit 96 participants (48 per centre) per group.

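### The primary analysis is labelled intention-to-treat but keeps only participants with complete 6-month data; the already planned repeated-measures model is the better primary analysis

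*Protocol article*

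**What the plan says.** All the relevant text is in the protocol article.

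- **Analysis set.** Data Collection/Management says that the primary analysis of primary and secondary outcomes is to be intention-to-treat, "based on a between-group comparison of intervention and control participants with complete data at 6 months".
- **Covariates.** The comparison is made "with adjustments being made for the baseline outcome score and centre". The 1- and 3-month outcomes do not enter it.
- **Rank of the alternative.** "In a secondary analysis we will extend the primary analysis model with a repeated measures comparison of groups at all follow-up points".
- **Missing data.** Patterns and reasons will be examined, and the investigators will "undertake appropriate imputation models to assess the impact of missingness on primary analysis models". Imputation therefore informs the primary result but does not produce it.
- **Attrition.** The Sample Size section allows for "a worst case attrition rate of 30% at 6-months follow up".
- **Earlier data.** Randomisation and Device Activation sets visits at 1, 3 and 6 months, with a multi-day pain diary brought to each.

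**The concern.** An intention-to-treat comparison keeps all randomised participants in the groups to which they were allocated. Requiring complete 6-month data removes some of them for a reason that arises after randomisation, and analysing the rest as allocated does not bring them back. A reader who sees the label would take the headline result to rest on the full randomised set.

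There is also a practical loss. Someone who leaves after month 3 has already supplied two post-randomisation diaries that predict the missing value, and the primary model uses neither. If leaving depends on those earlier scores, completers in the two arms may no longer be comparable given baseline and centre alone. A likelihood-based model over all visits with the same covariates is valid under that mechanism, and the protocol already plans a model over all visits. At stake are the primary estimate and P value of a trial whose stated purpose is to separate specific effects from placebo effects.

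**Working it through.** **1. The plan's own figure.** Inputs from Sample Size: the cited guidance "proposes a minimally important clinical difference (MICD) of 20 mm", with SD 25 mm, 90% power, 5% alpha (taken as two-sided) and 30% attrition.

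- Per arm: n = 2 × SD² × (1.960 + 1.282)² / difference² = 2 × 625 × 10.51 / 400 = 32.8, so 33.
- Inflated: 33 / 0.70 = 47.1, so 48 per arm and 96 in total.

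This matches the total of 96 in the Abstract. The words 'per group' after 96 in Sample Size do not fit the calculation; that is a separate point.

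**2. What the exclusion amounts to.** 0.30 × 96 = 28.8, about 29 participants excluded and about 67 analysed (33.6 per arm). Power in those completers is 90.6% (normal approximation) or 89.8% (t-test). The inflation protects power among completers but does nothing about bias.

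**3. Possible bias.** From the protocol: 48 per arm, true difference 20 mm, SD 25 mm, 30% dropout. Assumed: baseline SD 10 mm, baseline-outcome correlation 0.3, follow-up correlation 0.7 between adjacent visits (autoregressive), and loss after month 3 following logit(p) = intercept + slope × month-3 pain, with the intercept set to give the stated dropout. Slopes of 0.03 and 0.06 per mm are odds ratios of exp(0.75) = 2.1 and exp(1.5) = 4.5 per SD of 25 mm. The complete-case ANCOVA is compared with the sequential-regression (maximum-likelihood) estimator that uses months 1 and 3, over 3,000 to 5,000 replicates.

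| Dropout mechanism (30%) | Slope | Complete-case estimate | Bias | Complete-case power |
|---|---|---|---|---|
| Random | 0 | 20.2 mm | about 0 | 93% |
| Same slope, 30% lost in each arm | 0.06 | 20.1 mm | about 0 | 94% |
| One shared curve (loss 36% sham, 24% active) | 0.03 | 18.9 mm | 1.1 mm | 89% |
| One shared curve (loss 39% sham, 21% active) | 0.06 | 17.3 mm | 2.7 mm | 85% |
| Sham only, 30% lost in each arm | 0.03 | 16.9 mm | 3.1 mm | 81% |
| Sham only, 30% lost in each arm | 0.06 | 15.0 mm | 5.0 mm | 73% |
| Active only, 30% lost in each arm | 0.06 | 25.1 mm | 5.1 mm, overstating benefit | 99% |

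In every row the estimator using the earlier visits averaged 20.0 to 20.2 mm, with power of about 95% (based on its empirical standard error).

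**4. No true effect, 30% dropout.**

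- Dependence in one arm, slope 0.06: bias 5.0 mm, false-positive rate 14% (3.4 mm and 9% at correlation 0.5).
- Dependence in one arm, slope 0.03: 3.1 mm and 8%. Slope 0.02: 2.1 mm and 7%.
- Shared curve: bias about 0 and error rate about 5%.
- Estimator using the earlier visits: about 5% throughout.

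**5. Lower attrition.** At 10% dropout and slope 0.06, the bias is 1.4 mm (shared curve), 1.7 mm (sham only) and 2.0 mm (active only). One-arm dependence under no effect gives 1.8 mm and a 6% false-positive rate.

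**6. A milder set of assumptions.** This uses a common correlation of 0.5 to 0.7 among baseline and all visits, SD 25 mm throughout and a slope of 1 per SD. The bias is 1.4 to 1.6 mm for sham-only dependence, about 1 mm for pain-driven loss of 40% in sham and 20% in active, and about 0 for random dropout or for the same slope with equal loss.

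**The case against.** The strongest reply is that the protocol neither hides nor ignores the problem. It states the analysis set openly, plans the repeated-measures comparison, plans to examine why data are missing, and plans imputation to test the primary result. A material divergence would be visible. This stands as mitigation, but the headline estimate and P value would still be the complete-case ones. Statistical Methods defers detail to an analysis plan that is not shown, and that plan cannot be assumed to change a primary analysis fixed here.

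Three stronger readings are tempting, and the document does not support them.

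- *That outcome-related loss is documented.* Device Implantation and Device Repair or Removal name infection, SCS-related pain, patient withdrawal, hardware failure, lead migration, allergy and MRI. These are reasons for removing or repairing the device, not for losing follow-up, and nothing says that diaries stop at removal. All participants receive the same hardware before randomisation, so many of these events should arise similarly in both arms.
- *That 30% loss is expected.* The protocol calls it a worst case. The one retention figure shown, in the Introduction, is 65 of 72 implanted patients with data at 24 months, so 7 / 72 = 9.7% missing. That cohort was open-label and single-arm, so it is only indicative.
- *That serious bias is likely.* The larger figures need high attrition, steep dependence on pain and dependence in one arm only. All three are assumed.

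It is also fair that the alternative is not perfect. It requires missing-at-random, and participants with no follow-up diary remain excluded, so it is not a full intention-to-treat set either.

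**Conclusion.** The point holds and should be fixed. Two parts rest on the text alone: the intention-to-treat label does not describe a complete-data set, and the model that can use the 1- and 3-month diaries is ranked below one that cannot.

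The bias is possible, not established. With SD 25 mm, adjacent-visit correlation 0.7, 30% dropout and slopes of 0.03 to 0.06 per mm, it runs from about 0 mm (random dropout, or the same mechanism with equal loss) through about 1 to 3 mm (shared curve, true effect 20 mm) to about 3 to 5 mm (one arm only). One-arm dependence gives a false-positive rate of about 7 to 15% across the slopes and runs tried; weaker dependence or a more predictive baseline gives less bias. At 10% dropout the bias is about 2 mm or less. Its direction depends on which arm loses patients because of pain.

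The case for the swap does not depend on the worst figures. The estimator using the earlier visits recovered the true effect in every scenario tried, and the complete-case analysis did not. Dropout that depends on unobserved 6-month pain was not examined, and neither analysis is protected against it.

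**What to change.** Exchange the rank of two analyses that are already planned.

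- **Primary:** the repeated-measures model over 1, 3 and 6 months, adjusted for baseline score and centre, with the 6-month group contrast as the primary estimate. Analyse participants as allocated and include everyone with at least one follow-up diary. State this set outright: the article says only that "we will extend the primary analysis model with a repeated measures comparison of groups at all follow-up points", which could be read as inheriting the complete-data restriction.
- **Sensitivity:** the complete-case ANCOVA at 6 months, named as such and without the intention-to-treat label.
- **Imputation:** direct the planned work at departures from missing-at-random, including participants with no follow-up diary.

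The cost is wording in the protocol and analysis plan, settled before any unblinded analysis; Statistical Methods already places committee review of the analysis plan ahead of analysis. No new data or participants are needed. The downside is reliance on missing-at-random and a modelled covariance, and participants with no follow-up diary still drop out of the primary estimate. Their number by arm should be reported.

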**Methods:**

This is a multicentre, double-blind, randomised, sham-controlled trial with a parallel economic evaluation. A total of 96 patients with CNLBP who have not had spinal surgery will be implanted with an epidural lead and a sham lead outside the epidural space without a screening trial. Patients will be randomised 1:1 to 10 kHz SCS plus usual care (intervention group) or to sham 10 kHz SCS plus usual care (control group) after receiving the full implant. The SCS devices will be programmed identically using a cathodal cascade. Participants will use their handheld programmer to alter the intensity of the stimulation as per routine practice. The primary outcome will be a 7-day daily pain diary. Secondary outcomes include the Oswestry Disability Index, complications, EQ-5D-5 L, and health and social care costs. Outcomes will be assessed at baseline (pre-randomisation) and at 1 month, 3 months and 6 months after device activation. The primary analyses will compare primary and secondary outcomes between groups at 6 months, while adjusting for baseline outcome scores. Incremental cost per quality-adjusted life year (QALY) will be calculated at 6 months and over the lifetime of the patient.

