### Objectives

Hypothesis: The addition of 10 kHz SCS to usual medical care (intervention group) will provide superior back pain relief, compared to sham stimulation plus usual medical care (control group) for CNLBP.

Aim: The overarching aim of this study is to demonstrate the efficacy, safety and cost-effectiveness of 10 kHz SCS in the treatment of CNLBP with no prior surgery.

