### Device Implantation

Under standard operating theatre practice, all participants will be implanted with the following equipment: 10 kHz Senza IPG and two octopolar (8 contact) leads.

The first of the two leads will enter the epidural space through a lumbar or lower thoracic epidural puncture. The lead will be advanced cranially in the epidural space to reach a final position, where contacts 4 and 5 span the T9/10 disc space shown by Anterior-Posterior fluoroscopy in the anatomical midline as per our pilot experiment (Fig. 2). A lateral image will be obtained to ensure the lead is placed posteriorly in the epidural space.

Once satisfactory epidural lead placement is confirmed, the lead will be anchored to the deep fascia or supraspinous ligament and a strain relief loop will be established. The active epidural lead will be tunnelled to a subcutaneous pocket for the battery using an extension if necessary. This subcutaneous pocket is made in the gluteal region via a small skin incision and blunt subcutaneous dissection. This pocket should be large enough to accommodate the IPG, extensions and sham lead. This active lead (AL) will be used to provide therapy to the intervention group. The AL will be connected to the first or top port of the IPG in all participants, and a second sham lead (SL) will be inserted subcutaneously and attached to the second port of the IPG (Fig. 3). Impedances to check electrical integrity of the system will be performed at this time. Information will be given about wound care, and the device will remain ‘off’ until the participant’s next visit. Removal of sutures (if necessary) will be done at the implantation site.

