### Randomisation and Device Activation

The randomisation and device activation visit will take place between 2 and 4 weeks post-implantation, pending proper wound healing.

Firstly, the following will be performed by blinded study personnel:
Participants will be assessed to determine whether they have experienced any adverse events, and a case report form (CRF) will be completed, as applicable.New x-ray images will be taken to record the lead locations.Participants will be provided with a multi-day diary and instruct to record their VAS pain scores daily for 7 days prior to the 1-month follow-up.The participant’s device and lead will be programmed according to their allocated group; whereas the lead is different, the programming parameters used are identical and can be found in Fig. 2.

At this point, the participant enters the ‘follow-up’ phase of the study, with visits at 1, 3 and 6 months. These visit frequencies mirror our standard of care for routine clinical practice.

During these visits, all participants will be asked to complete the following questionnaires in addition to bringing their multi-day pain diary:
Pain severity on a 0-100 mm (VAS)Pain mapOswestry Disability Index (ODI v2.1a)Patient Health Questionnaire 9 (PHQ-9)Pittsburgh Sleep Quality Index (PSQI)EQ.5D-5 LPain medication usagePatient Global Impression of Change (PGIC)Participant satisfactionSensation map.

Any adverse events are monitored and documented in the CRF. An X-ray may be taken if there are any concerns about lead migration.

To check fidelity of blinding, participants and assessors will be asked to guess their treatment allocation at the end of the study. We will monitor potential outcome assessor blinding by asking them to guess each patient’s allocation at the end of each follow-up assessment. After the trial is completed, we will compare actual and anticipated treatment allocations.

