### Harms

#### Foreseeable Adverse Events and Anticipated Adverse Device Effects

We expect the risk of serious adverse events to be rare, and our results from the previous 10 kHz stimulation trial showed the risk of adverse events to be as follows:
Battery pocket pain 8%Wound infection 3%Electrode migration 5%Lead Fracture or malfunction 6%Headache from epidural puncture 1%Nerve injury < 1%Spinal cord haematoma and abscess < 1%Unwanted, perceived stimulation < 1%

Pocket pain is usually self-limiting within 6 months, and electrode migration is mitigated using cascade stimulation programming. Wound infection will necessitate the removal of the device. In some instances the system will require repair or removal. The reasons for this include infection, hardware displacement, pain or discomfort from the device, or device failure. The risks are similar to those mentioned above.

All adverse events will be recorded and reported in accordance with Good Clinical Practice.

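### The only safety analysis named compares randomised groups, so its contrast isolates stimulation, and a participant explanted before randomisation has no place in it

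*Protocol article*

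**What the plan says.** **Aim.** The Objectives section of the protocol article sets out to "demonstrate the efficacy, safety and cost-effectiveness of 10 kHz SCS in the treatment of CNLBP with no prior surgery".

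**Order of events.** The abstract (Methods) has participants allocated to the intervention or the "control group) after receiving the full implant". Under Device Implantation, "all participants will be implanted with the following equipment: 10 kHz Senza IPG and two octopolar (8 contact) leads". Under Randomisation and Device Activation, "The randomisation and device activation visit will take place between 2 and 4 weeks post-implantation, pending proper wound healing".

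**Safety analysis.** Secondary Outcomes lists a comparison of complications and adverse events between intervention and control, timed at 6 months post-randomisation. Data Collection/Management adds "Safety outcomes will be reported descriptively by group". No other safety summary is named, and none is described for all implanted participants.

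**Foreseeable harms.** The Harms section expects pocket pain in 8%, wound infection in 3%, electrode migration in 5%, lead fracture or malfunction in 6% and puncture headache in 1%. It puts nerve injury, spinal haematoma or abscess, and unwanted stimulation each below 1%. It also states "Wound infection will necessitate the removal of the device".

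**Capture of events.** Adverse events are checked and entered on a case report form at the randomisation visit. The Harms section commits to recording and reporting all adverse events under Good Clinical Practice.

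**The concern.** Two features of the design bear on the named analysis.

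First, surgery is identical in both groups and comes before allocation. A comparison of the groups therefore carries no information about harm caused by the surgery or by the presence of the hardware. Most of the foreseeable harms listed are of that kind; unwanted stimulation is the only one that plainly belongs to the current being delivered. A report of no difference in complications would answer a narrower question than the aim poses.

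Second, reaching randomisation depends on wound healing, and infection leads to removal. A participant whose device is removed in the 2 to 4 weeks before activation is never allocated, so a table laid out by group has no column for that person. The omission is selective, because the harm itself causes it. Infection and removal rates read from the by-group table would then be too low as estimates for people who undergo the implant.

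**Working it through.** **Inputs**
- Number implanted: 96 in total (abstract, Methods).
- Wound infection rate: 3% (Harms).
- Consequence of infection: device removal (Harms).
- Interval from implant to randomisation: 2 to 4 weeks, dependent on healing (Randomisation and Device Activation).
- Share of infections leading to removal before randomisation: not stated. Assumed here at 25%, 50%, 75% and 100%.

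**Step 1: the plan's own figure.** The inputs under Sample Size are a difference of 20 mm, SD 25 mm, 90% power and 5% alpha (taken as two-sided), and 30% attrition.

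n per group = 2 × (1.960 + 1.282)² × (25/20)² = 2 × 10.507 × 1.5625 = 32.8, so 33.

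After attrition, 33/0.70 = 47.1, so 48 per group and 96 in total. The abstract's 96 is reproduced and is used as the denominator below. The Sample Size section attaches 96 to each group, which its own inputs do not support.

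**Step 2: the contrast.** Write the risk of a given event as a common part due to the implant, plus a part added by active epidural stimulation in the intervention arm. The common part has the same expected value in both arms because surgery precedes randomisation. The expected difference due to the implant alone is 0, whatever its true rate. The common part stays in each arm's own rate.

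**Step 3: expected events among 96 implanted.**
- Pocket pain: 0.08 × 96 = 7.7
- Wound infection: 0.03 × 96 = 2.9
- Electrode migration: 0.05 × 96 = 4.8
- Lead fracture or malfunction: 0.06 × 96 = 5.8
- Puncture headache: 0.01 × 96 = 1.0

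**Step 4: participants with no group.** With share f of infections leading to removal before randomisation, the expected number is 96 × 0.03 × f, and the chance of at least one is 1 − (1 − 0.03f)^96.

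| f (assumed) | Expected with no group | Chance of at least one |
|---|---|---|
| 25% | 0.72 | 1 − 0.9925^96 = 51% |
| 50% | 1.44 | 1 − 0.985^96 = 77% |
| 75% | 2.16 | 1 − 0.9775^96 = 89% |
| 100% | 2.88 | 1 − 0.97^96 = 95% |

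If 96 per group (192 in total) were implanted, the expected numbers would double to 1.4 to 5.8.

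**Step 5: precision of a pooled summary.** As an illustration, 3 infections among 96 implanted is 3.1%, with an exact (Clopper-Pearson) 95% confidence interval of 0.6% to 8.9%.

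**The case against.** The strongest reply is that this is detail for the statistical analysis plan, which the protocol promises and which is not shown. It may well define a safety set of all implanted participants, and the sentence in Data Collection/Management does not rule one out. That stands as a limit. The point does not rest on silence alone, however: the protocol fixes its safety outcome as a comparison of randomised groups, and that does not match an aim covering the safety of the treatment.

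A reader might infer three stronger things, and the documents support none of them.

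- *That safety is counted only from randomisation, so early events are lost.* Secondary Outcomes gives a time point for the comparison, not a start of counting. Events since implantation are recorded at the randomisation visit, and all adverse events are to be reported. For anyone then randomised, an early event can appear in the by-group table.
- *That implant harms cancel and so become invisible.* They cancel only in a difference. Reporting is descriptive, so each arm's rate would show them in randomised participants. Pocket pain, migration and lead failure can also arise after activation.
- *That the table would show 0/93 against a true 3/96.* This needs every expected infection to lead to removal before randomisation, which is the extreme of a range the protocol does not pin down.

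Isolating the specific effect of stimulation is, moreover, what the sham design is for. The participant flow figure is not shown either, so it may already count people implanted but not randomised. Even so, a flow count gives no event rates.

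**Conclusion.** The point holds in a limited form. The weakness lies in the named analysis, not in data collection, and the efficacy analysis is untouched. The by-group contrast speaks only to the added harm of active epidural stimulation over sham. The by-group table also has no place for a participant explanted or not healed before randomisation.

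The expected omission is about 0.7 to 2.9 participants out of 96, with a 51% to 95% chance of at least one. This rests on the protocol's 3% infection rate, on its statement that infection leads to removal, and on an assumed 25% to 100% of infections leading to removal before randomisation. The numbers are small, but the omission is selective and concerns a harm that a safety aim should count. It is worth correcting before analysis.

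**What to change.** Keep the by-group table and make three changes in the protocol or the analysis plan.

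1. Define a safety set of everyone in whom implantation was started, whether or not they were later randomised. Summarise procedure- and device-related events in that set, pooled over groups and counted from implantation, with exact 95% confidence intervals.
2. Label the between-group comparison as the effect of stimulation only.
3. Unless the flow diagram already does so, show in it the number implanted but not randomised, with reasons.

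The cost is one additional table and a few lines of text, built from events already recorded. No new visits, data items or clinical rules are needed.
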